**2. The distance that Strep A droplets move beyond a suspected infection**

These experiments will be completed at two time points: 24 hours post-challenge and 48 hours post-challenge, commencing at 09 : 00 on Days 2 and 3, respectively. Participants will be seated on their beds in front of a table draped with a sterile mat and adjusted to be the same height as their chest. The table will be exactly 30 centimetres (cm) from the chest of the participant and will hold the HBA-CNA settle plate (Fig. 1). To understand transmission during speaking, the participant will be asked to count upwards from one in a conversational tone for one minute as recorded by a stopwatch. At the conclusion of the minute, the participant will cease counting, and the plate will remain in place for an additional minute to capture any droplets that may still be falling. The experiment will be repeated in the manner described above with new plates placed at distances of 90 and 180cm [14, 28].

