### Study objectives

The primary objective of this sub-study within CHIPS is to assess the transmission potential of Strep A in a clinical environment, where the timing and infective dose of Strep A causing potential pharyngitis are pre-defined. Secondary objectives include determining the distance of Strep A droplet spread during conversation, investigating potential airborne spread of Strep A, and the isolation of Strep A from hard and soft surfaces in the clinical environment. It is also anticipated that this sub-study may allow for determination of the impact of different doses of treatment with penicillin against the transmission potential of Strep A.

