### Sample size

The CHIPS Trial will be recruiting 60 participants as dictated by sample size calculations [31]. For this pilot sub-study, a formal sample size calculation has not been performed. Instead, a pragmatic approach dictated by resource and personnel constraints has been adopted and up to 20 participants will be enrolled. All participants will consent to participate in the sub-study at the time of trial enrolment and will provide verbal consent to participation at the first time point (24 h post-challenge).

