### Microbiological analysis

All swabs and CNA plates collected will undergo transfer and processing for microbial culture for beta-haemolytic streptococci (BHS) using gold standard culture methodology [35] and according to Clinical and Laboratory Standards Institute (CLSI) standards. If no bacterial growth is observed after 24 hours, incubation will be extended for a further 24 hours to allow growth of slow-growing or small colonies. The presence of Strep A as indicated by β-haemolytic morphology will be confirmed with subculture, bacitracin sensitivity testing and positive group A latex agglutination reaction (Streptex, Thermo Scientific). Strep A isolates will be stored at −80 °C to permit further strain characterization. Results will be reported as the presence or absence of Strep A on each sample. Quantitation of the amount of Strep A is not possible with this experimental design.

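### Experiment 2 runs the nearest distance first and describes no varied order or clearance between runs, so distance is aligned with run order and small particles left from an earlier run could be read as direct reach

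*Protocol article*

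**What the plan says.** The procedure is in the protocol article, Study procedures, experiment 2.

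- **First run.** "The table will be exactly 30 centimetres (cm) from the chest of the participant and will hold the HBA-CNA settle plate". The participant is asked to "count upwards from one in a conversational tone for one minute as recorded by a stopwatch". When the counting stops, "the plate will remain in place for an additional minute to capture any droplets that may still be falling".
- **Later runs.** "The experiment will be repeated in the manner described above with new plates placed at distances of 90 and" 180 cm. The Fig. 1 caption lists the distances as (a) 30, (b) 90 and (c) 180 cm.
- **Sessions.** "These experiments will be completed at two time points: 24 hours post-challenge and 48 hours post-challenge". One description serves both.
- **Size.** Under Sample size, "up to 20 participants will be enrolled".

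Under Study objectives, a secondary objective is "determining the distance of Strep A droplet spread during conversation"; airborne spread is listed as a separate one. Under Microbiological analysis, "Results will be reported as the presence or absence of Strep A on each sample", and the same section rules out quantitation.

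The article describes no varied order, no clearance interval between runs and no blank plate between runs. The Discussion treats contamination between participants and the 180 cm ceiling as limitations, but does not mention run order or carry-over from one run to the next.

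**The concern.** The distance objective rests on comparing three plates within the same participant. If the nearer plate always comes earlier, the farther plates are opened in air that already holds material from the earlier counting, and distance cannot be separated from position in the sequence.

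The extra minute of plate dwell shows that the authors expect material to be falling after speech ends. It suits large droplets. Smaller particles can outlast it, drift, and settle on the next plate. A positive plate at 180 cm could then mean either that one minute of talking sent droplets that far, or that residue from an earlier run arrived there. Because results are presence or absence only, one carried-over colony scores the same as heavy direct deposition, so the data cannot show which happened. The Discussion reports that earlier work found little spread at any distance from talking, so a few positive far plates would be the notable result and the one hardest to interpret.

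**Working it through.** The plan states no figure on this point, so there is none to reproduce. The check has three parts.

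**1. Timeline, from the text.** Each run is 1 min of speech plus 1 min of dwell. With the shortest possible changeover (zero; the article gives none) and the order 30, 90, 180 cm:

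| Run | Distance | Speech (min) | Dwell (min) |
|---|---|---|---|
| 1 | 30 cm | 0–1 | 1–2 |
| 2 | 90 cm | 2–3 | 3–4 |
| 3 | 180 cm | 4–5 | 5–6 |

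When the 180 cm plate opens at minute 4, material from run 2 is at least 60 s old and material from run 1 at least 180 s old.

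**2. What is still airborne (assumptions, not in the documents).** Still air, Stokes settling, density 1000 kg/m³, viscosity μ = 1.81 × 10⁻⁵ Pa·s, mouth-to-plate fall h of 0.2 to 0.5 m. Settling speed is v = ρgd²/(18μ), so the largest particle not yet settled after time t has diameter d = √(18μ(h/t)/(ρg)).

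- t = 60 s: d = 10.5 µm (h = 0.2 m), 12.9 µm (0.3 m), 14.9 µm (0.4 m), 16.6 µm (0.5 m).
- t = 180 s, h = 0.3 m: h/t = 1.67 mm/s, so d is about 7.4 µm.
- Time to fall 0.3 m: 50 µm, about 4 s; 20 µm, 25 s; 10 µm, 100 s; 5 µm, 399 s.

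One minute therefore clears large droplets but not particles below roughly 10 to 17 µm.

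**3. What a small carry-over rate would do (illustration only).** Let c be the chance that an earlier run leaves a colony on the 180 cm plate. Take it as equal and independent for the two earlier runs, and suppose nothing reaches 180 cm directly. Then P(positive plate) = 1 − (1 − c)², and P(at least one among 20 participants in one session) = 1 − (1 − c)⁴⁰.

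| c (assumed) | One 180 cm plate | At least one of 20 |
|---|---|---|
| 0 | 0 | 0 |
| 0.02 | 0.040 | 0.55 |
| 0.05 | 0.098 | 0.87 |
| 0.10 | 0.190 | 0.99 |

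The documents give no value for c, and equal c for both runs is generous because run 1 material is older. The table shows only that a presence/absence result over 20 participants is sensitive to rare carry-over. It does not estimate how often carry-over occurs.

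**The case against.** **The order may not be fixed.** The text puts 30 cm first but does not say that 90 precedes 180, that the sequence is the same for everyone, or how long passes between runs. The stated minute is plate dwell, not the gap. The full CHIPS protocol is not shown and may say more. This stands as a limit: the point concerns the procedure as printed.

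**Residue is still reach.** Material left from an earlier run was emitted while talking and did arrive at 180 cm. That is fair. What is lost is the attribution to direct droplet throw during that run. This matters because the objectives list droplet distance and airborne spread as separate questions.

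**The planned comparisons are safe.** Statistical analysis relates each result to penicillin dose and to pharyngitis status. These are comparisons between participants, and an order common to all does not bias them. This stands in full.

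**Stronger readings that the documents do not support.**

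- A reader might infer that the 180 cm plate samples three minutes of speech instead of one, and so up to three times the material. That would need everything from both earlier runs to stay airborne. By the settling figures above (0.3 m fall, no changeover), only particles below about 7.4 µm from run 1 and about 13 µm from run 2 remain. A 5 µm particle falls at 0.075 cm/s, only about 9 cm in the plate's 120 s exposure.
- A reader might also infer that a negative far plate could be a late-session effect of a drying mouth or fatigue. Nothing in the documents supports this for three one-minute counts, and carry-over cannot turn a plate negative.

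**Reordering alone is not a cure.** Randomising moves carry-over to whichever distance comes later. This stands, and is why the fix also needs a gap and separate reporting of plates exposed first.

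**Conclusion.** The point holds as a weakness of moderate weight in one secondary objective of a pilot sub-study. As printed, 30 cm comes first, the farther distances follow as separate runs, and neither a varied order nor a clearance interval is described. Distance is then aligned with run order, and a positive far plate cannot be cleanly attributed to direct reach.

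The mechanism is limited to small particles, below roughly 10 to 17 µm at 60 s under still air and an assumed 0.2 to 0.5 m fall. Room air movement, the true changeover time and the amount of viable organism in such particles are all unknown, so the size of the carry-over cannot be derived. If every far plate is negative, carry-over has done no harm. That 90 cm precedes 180 cm is an inference from the wording and the caption.

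**What to change.** - **Order.** Counterbalance or randomise the three distances across participants and sessions, and record the order used. There are 6 possible orders. With 18 participants each is used 3 times in a session; with 20, each is used 3 or 4 times. The 180 cm plate comes first in 2 of the 6, so 6 to 8 of 20 participants per session would supply a 180 cm plate with no earlier counting run in that session.
- **Clearance.** State a fixed gap between runs. As an example, a 2-minute gap means that at least 180 s pass between the end of speech and the next plate, which lowers the still-air cut-off from about 13 to about 7.4 µm at a 0.3 m fall.
- **Reporting.** Describe distance within participant, and show separately the far plates that were exposed first.
- **Alternative.** Where space allows and the nearer table does not obstruct the farther plates, expose all three during one counting minute and its settling minute. This removes both order and carry-over between runs. The Discussion notes limited space in the facility, so it may not be feasible.

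The cost is a printed order list and a few more minutes: a 2-minute gap between three runs adds 2 × 2 = 4 minutes to a session of at least 3 × 2 = 6. No extra plates or participants are needed.

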**Fig. 1. F1:**
[figure not shown]
A graphical depiction of transmission experimentation with agar plates placed (**a**) 30 cm, (**b**) 90 cm and (**c**) 180 cm from the chest of the participant as they count from 1 to 100 for one minute.

**3. The environmental assessment of the confinement room via swabbing**

Following the completion of the droplet transmission experiments, environmental swabs of five items belonging to each participant will be collected. These will include one personal item as determined by the participant, the bed remote control, bedside table, water bottle/cup and intravenous (IV) stand. Flocked swabs (Conan regular flocked swab breakpoint in peel pouch sachet; Copan, Italy) selected for appropriateness of use and transport with our selected medium will be moistened with two to three drops of sterile saline and rolled over the selected object/surface in at least two different diagonal directions across a surface area of approximately 25 cm^2^. Swabs will be placed immediately in a cryovial containing 0.5 ml of skim milk, glucose, glycerol broth (SGGB) solution (PathWest Media) kept at 4–8 °C. In addition, 10 common, high-touch areas in the confinement room will be swabbed using the same methodology, selected based on observation of the room during morning vital checks. A timeline demonstrating when each experiment will occur can be seen in Fig. 2.

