## Abstract

*

Streptococcus pyogenes

* (also known as group A *

Streptococcus

*, Strep A) is an obligate human pathogen with significant global morbidity and mortality. Transmission is believed to occur primarily between individuals via respiratory droplets, but knowledge about other potential sources of transmission via aerosols or the environment is limited. Such knowledge is required to design optimal interventions to control transmission, particularly in endemic settings. We aim to detail an experimental methodology to assess the transmission potential of Strep A in a clinical environment. We will examine potential sources of transmission in up to 20 participants recruited to the Controlled human infection for penicillin against *
Streptococcus pyogenes* (CHIPS) Trial. Three approaches to understanding transmission will be used: the use of selective agar settle plates to capture possible droplet or airborne spread of Strep A; measurement of the possible distance of Strep A droplet spread during conversation; and environmental swabbing of personal and common high-touch items to detect the presence of Strep A on hard and soft surfaces. All methods are designed to allow for an assessment of transmission potential by symptomatic, asymptomatic and non-cases. Ethical approval has been obtained through Bellberry Human Research Ethics Committee (approval 2021-03-295). Trial registration number: ACTRN12621000751875. Any results elicited from these experiments will be of benefit to the scientific literature in improving our knowledge of opportunities to prevent Strep A transmission as a direct component of the primordial prevention of rheumatic fever. Findings will be reported at local, national and international conferences and in peer-reviewed journals.

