Existing evidence points to the transmission of Strep A primarily by large respiratory droplets [14–16]. Contemporary methods have worked to verify this and through the use of biological swabs, environmental swabs and environmental settle plates have suggested other mechanisms, including small droplet (nasal secretions, sputum or spit) [17, 18], skin-to-skin contact [19, 20], direct contact with bedding, fabrics and surfaces [21, 22], and via food [23, 24] and insects [25–27]. A study completed in the United Kingdom (UK) during a recent scarlet fever outbreak suggested the potential for Strep A to be disseminated via the airborne route, as measured by the placement of settle plates at various heights above the droplet-generating potential of small children [28]. Research in clinical settings has also used settle plates to identify transmission during outbreaks of Strep A causing invasive disease [29]. While verification of many of these transmission mechanisms is still required, it is acknowledged that the type of spread from infected to uninfected individuals may vary according to the clinical manifestation of infection [30].

This protocol, embedded in a human challenge study evaluating the minimum concentration of penicillin required to prevent pharyngitis infection [31], defines the experimental methodology we designed to further understand the transmission potential of Strep A pharyngitis in a controlled setting.

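### Isolating Strep A from soft surfaces is a stated objective, but the swab list guarantees no soft-surface sample

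*Protocol article*

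**What the plan says.** Three places in the protocol article bring in soft surfaces.

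- Study objectives lists as a secondary objective "the isolation of Strep A from hard and soft surfaces in the clinical environment".
- The Abstract names swabbing as the means: "environmental swabbing of personal and common high-touch items to detect the presence of Strep A on hard and soft surfaces".
- The Introduction, summarising earlier work on suspected routes, includes "direct contact with bedding, fabrics and surfaces".

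The sampling is set out in Study procedures, experiment 3. There, "environmental swabs of five items belonging to each participant will be collected", and the list follows: "These will include one personal item as determined by the participant, the bed remote control, bedside table, water bottle/cup and intravenous (IV) stand". In addition, "10 common, high-touch areas in the confinement room will be swabbed using the same methodology, selected based on observation of the room". One technique serves every site: the moistened swab is "rolled over the selected object/surface in at least two different diagonal directions across a surface area of approximately 25 cm^2". Under Sample size, "up to 20 participants will be enrolled".

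The Discussion says that the beds stand in a shared ward and are separated by curtains, which participants keep closed. No curtain, bedding or clothing is named as a swab site anywhere in the article.

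**The concern.** The objective covers two kinds of surface, and the list that is meant to serve it fixes only one kind. The team could follow experiment 3 to the letter and finish without a single fabric sample.

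Any soft samples that do arise would come from a participant's choice or from observation on the day. Their number, their kind and how they were exposed would then vary between participants. Statistical analysis plans to set presence or absence of Strep A against penicillin dose and against diagnosed pharyngitis. For soft surfaces there would be no assured set of samples, and no consistent one, on which to do that. The Discussion also hopes to learn whether standard infection control without physical isolation is adequate in a curtained ward. A negative surface result that happened to include no curtain or bedding would be weak support for that.

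**Working it through.** The plan states no figure on this point, so there is nothing to reproduce. The check classifies the named sites by surface type and counts them.

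**Inputs**
- Participants: 20, the upper limit under Sample size.
- Items per participant: 5 (experiment 3).
- Common areas: 10 (experiment 3). The text does not say how often they are swabbed. The count below assumes once per round.
- A round is one swabbing session for every participant. The text places swabbing after the droplet experiments, which run at 24 and 48 hours, and does not say plainly whether there is one round or two. All counts are therefore per round.

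**Is the item list complete?** The list opens with a verb that could signal examples only. But the preceding sentence promises five items and exactly five are then given, so it reads as complete.

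**Classification**

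| Site | Per round at 20 participants | Surface type |
|---|---|---|
| Bed remote control, bedside table, water bottle or cup, IV stand | 4 × 20 = 80 | fixed, hard |
| Personal item chosen by the participant | 1 × 20 = 20 | not specified |
| Common high-touch areas | 10 | not specified |
| Total | 110 | |

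**Result**
- Participant swabs fixed on hard items: 80 / 100 = 80%.
- All swabs fixed on hard items: 80 / 110 = 73%.
- Soft swabs guaranteed: 0.
- Soft swabs possible: 0 to 20 personal plus 0 to 10 common, so 0 to 30.
- Soft sites common to all participants: none.

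**What one fixed soft item per participant would give.** Swapping one hard item for a soft one leaves 3 × 20 = 60 fixed hard swabs and adds 1 × 20 = 20 fixed soft swabs, with the total unchanged at 110. To show what 20 samples can say, suppose that all are negative. The exact binomial upper limit for 0 positives in n is 1 − α^(1/n):
- one-sided 95%: 1 − 0.05^(1/20) = 13.9%;
- two-sided 95%: 1 − 0.025^(1/20) = 16.8%.

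These limits treat the 20 swabs as independent with one common positive rate. Participants receive different penicillin doses, so the limits indicate scale only. They also concern detection by this swab method, not presence on the fabric.

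**The case against.** The strongest reply is that experiment 3 leaves two routes open to soft surfaces. A participant may choose something made of fabric, and the 10 observed high-touch areas may well include a curtain edge, a chair or bedding. The objective is isolation, so one positive soft sample would meet it without any fixed denominator. This stands. A reader might infer that the soft-surface question cannot be answered at all, and the article does not support that.

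Two other inferences also go too far.
- A reader might object that hard and soft positivity could not be compared. The article promises no such comparison; it names only dose and pharyngitis status.
- A reader might fear that negative results would be reported as covering both surface types when only hard ones were swabbed. Microbiological analysis says results are reported for each sample, so every result stays tied to its item, and the fear is speculation.

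It is also fair to say that the Introduction's mention of bedding summarises literature and is not a commitment to sample it, and that this is a small pilot.

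The appeal to a fuller trial protocol carries less weight. The article does not leave the participant list out. It gives the list in full, and that list does not match the objective. Nor can a later analysis plan supply samples that were never taken. Pilot status explains the absence of a sample size calculation, but not a sampling list that leaves half of an objective to chance.

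**Conclusion.** The point holds in a limited form: soft-surface sampling is not assured. At 20 participants, each round has 80 fixed hard swabs, no fixed soft swab, and 20 personal plus 10 common swabs whose surface type is left open. The soft-surface yield can be anything from 0 to 30, with no consistent soft site across participants.

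This rests on reading the five listed items as complete, on all 20 places being filled, and on the 10 common areas being swabbed once per round. With fewer participants or another schedule for the common areas the upper end moves, but the guaranteed number of soft swabs remains 0. The defect affects one part of one secondary objective. It is worth correcting before sampling because correction costs almost nothing then and is impossible afterwards.

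**What to change.** Within the existing swab count:

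1. Require at least one fabric site, for example a dividing-curtain edge, among the 10 common areas.
2. Preferably, also name one fixed soft item per participant, for example the pillowcase or top sheet, in place of one of the four hard items, with the same swab technique and area. Together these raise the guaranteed soft swabs from 0 to 20 + 1 = 21 per round at 20 participants.
3. Record the surface type of every swab, including the participant's chosen item, and report hard and soft results separately.

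If no soft site is fixed, delete the reference to soft surfaces from the Abstract and from Study objectives.

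The change needs no extra swabs, staff or visits. Its price is one hard item per participant, or one common site, no longer sampled. A flocked swab may also recover less from fabric than from a hard surface, so negative soft results should carry that caveat. The first and third steps alone are the lighter option: they keep all four hard items but guarantee only one soft swab per round.
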